## Abstract

Recent advances in the study of the gut microbiota has pointed to its under-utilized source of potentially beneficial bacteria, known as next generation probiotics, offering a promising avenue to restore or compensate impaired gut microbiota toward a healthy state. Aside from the difficulties to achieve in-lab adequate culture conditions, the use of beneficial bacterial isolates is also limited by their bioavailability in the donor itself. In the iTARGET study, we positively selected donors based on their diet enriched in fiber, that has been shown to increase the prevalence of bacterial species associated with health.

The iTARGET study is a monocenter, prospective, observational study of adults with healthy lifestyle and high daily fiber consumption. We aim to recruit individuals in two phases, the first one for all individuals that will permit the identification of carriers for bacteria of interest and the second phase for a subset of individuals to allow for culture and isolation of previously identified potentially beneficial bacteria. Our primary outcome is the isolation and culture of at least one potentially beneficial isolate. The secondary outcomes comprised the high throughput metagenomic profiles of the intestinal microbiota and the characterization of the cultured isolates.

The study was approved by the French Research Ethics Committees (Comité de Protection des Personnes Sud-Est I) under the National reference ID 2023-A01677–38. Study findings and results will be published in peer-reviewed Open Access journals. (Trial registration number on ClinicalTrials.gov: NCT06166810).

Specifications table

**Table utbl0001:** 

Subject area:	Food Science
More specific subject area:	Positive selection of healthy donors with high fiber diet consumption
Name of your protocol:	iTARGET study protocol
Reagents/tools:	Not applicable
Experimental design:	The iTARGET cohort is a monocenter, prospective, observational study of adults with healthy lifestyle and high daily fiber consumption.
Trial registration:	NCT06166810
Ethics:	The study was approved by the French Research Ethics Committees (Comité de Protection des Personnes Sud-Est I) under the National reference ID 2023-A01677–38. Written Informed consent will be obtained from each participant before enrollment.
Value of the Protocol:	• This study is based on the positive selection of donors with healthy lifestyles and fiber-rich dietary profiles to provide stools for which we aim to isolate potentially beneficial bacteria. • The collection of stools associated with dietary profiles and omics profiles will provide a unique bioresource for the isolation of potentially beneficial bacteria. • The culture of isolates will permit the definition of optimized conditions to achieve their in vitro cultivation for a wide range of potentially beneficial bacteria and the characterization of the isolates will permit to validate their interest as potentially beneficial bacteria.

## Background

Over the past decades, numerous studies have been performed to gain a better understanding on the role of the intestinal microbiota in human health [1,2]. The gut microbiota, that is the complex and dynamic set of microorganisms colonizing our gastrointestinal system, have been shown to play a crucial role in health and disease, including human digestive, metabolic, immune and neurological functions [3,4]. An imbalance of the gut microbiota, known as dysbiosis, is frequently described in chronic diseases or metabolic dysfunctions in humans [[5], [6], [7]]. In many pathologies, this qualitative or quantitative alteration of the gut bacteria is responsible for its detrimental effect on anti-inflammatory bacterial species, often concomitant to the rises of pro-inflammatory species, ultimately modulating the structure and functionalities of the gut microbial community. Therefore, there is a major interest to directly exploit potentially beneficial bacteria as new-generation probiotics, and/or explore their functionalities, in order to restore or compensate impaired alteration of the gut microbiota toward a healthy state [8,9].

Among the factors influencing this intestinal balance, diet plays a predominant role [[10], [11], [12], [13]]. Mounting evidence from epidemiological studies have highlighted the positive impact of a diet rich in plant sources on human health, including obesity, type 2 diabetes or population at risks of cardiovascular diseases [[14], [15], [16], [17]]. More specifically, the consumption of fruit, vegetables, pulses and whole grain cereals is associated with health and, in particular, with an increase in the relative abundance of potentially beneficial bacterial species [10]. In this context, the modulation of the intestinal microbiota directly via the diet, by providing specific substrates to certain bacterial groups, or directly through the intake of these beneficial bacteria, the so-called next generation probiotics, is therefore a possible promising approach to the prevention and/or treatment of pathologies.

To date, a large number of bacterial species from the intestinal microbiota have yet to be isolated and cultured, limiting the characterization of their potential health benefits. The difficulties in isolating and culturing bacteria from the intestinal microbiota are linked to (i) the optimal culture conditions that are generally unknown and the continuity of the anaerobic conditions, (ii) the methods for isolating bacteria, generally relying on non-targeted approaches and undefined media, and (iii) the strategies for selecting the donors. Bacterial species positively associated with health have been identified using *in silico* metagenomic analysis by comparing healthy individuals and patients confronted to their respective diet [18,19]. In order to isolate and cultivate these beneficial bacteria, individuals with diet enriched in fiber are therefore particularly relevant. In this context, a positive selection of donors based on their dietary profiles is essential to favor the prevalence of these beneficial bacteria. To the best of our knowledge, no study has yet used positive donor selection to isolate new bacterial species with healthy potentials and associated to the consumption of fiber.

### Description of protocol

**Study aims**

The primary aim of the study is to isolate bacteria from stools of participants on a high-fiber diet, comprising new isolates of known species (list of selected species in Table 1) or new species for which no isolates have yet been cultured (Fig. 1). The secondary objectives of the study are (i) to characterize the microbiota of the recruited participants in order to identify carriers for bacteria of interest in relation to their diet, and (ii) to characterize isolated bacteria at the phenotypic and genotypic levels.

**Table 1 tbl0001:** Selected bacteria of interest for their isolation and culture in the iTARGET study [20].

Bacterial strain (GTDB taxonomy)	NCBI accession number	Interest	References
*Akkermansia muciniphila* DSM 22,959	GCF_000020225.1	Metabolic syndrome	[21,22]
*Bifidobacterium adolescentis* DSM 20083T	GCF_000010425.1	Intestinal barrier	[23]
*Bifidobacterium bifidum* NCTC 13,001	GCF_900,637,095.1	Colitis	[24]
*Bifidobacterium longum* spp.	GCF_000020425.1 and GCF_900,637,335.1	Gut-brain axis	[25]
*Phocaeicola vulgatus* ATCC 8482	GCF_000012825.1	Diet induced hepatic steatosis	[26]
*Bacteroides intestinalis* DSM 17,393	GCF_000172175.1	Primary polysaccharides degrader	[27]
*Bacteroides fragilis* NCTC 9343 (EN-2)	GCF_000025985.1	Primary polysaccharides degrader	[28]
*Bacteroides thetaiotaomicron* DSM 2079T	GCF_000011065.1	Primary polysaccharides degrader	[28]
*Bacteroides xylanisolvens DSM 18836T*	GCF_000273315.1	Pasteurized milk product fermented with B.xylanisolvens approved as novel food	[29]
*Bacteroides uniformis* ATCC8492	GCA_000154205.1	Post-antibiotic recovery	[30]
*Anaerostipes hadrus* BPB5	GCF_001998765.1	Butyrate producer	[31]
*Anaerostipes caccae* DSM 14,662	GCF_000154305.1	Food allergy	[32]
*Coprococcus eutactus* ATCC 27,759	GCF_000154425.1	Colitis	[33]
*Coprococcus catus* AF45–17	GCF_003433855.1	Short Chain fatty acid producer	[34]
*Coprococcus comes* ATCC 27,758	GCF_000155875.1	Chronic musculoskeletal pain(fibromyalgia)	[35]
*Roseburia intestinalis* DSM 14,610 (L1–82)	GCF_000156535.1	Polysaccharides degraders	[36]
*Roseburia inulinivorans* 2789STDY5608835	GCF_001406675.1	Metabolic syndrome	[36]
*Butyrivibrio crossotus* DSM 2876	GCF_000156015.1	Healthy diet positive association	[37]
*Ruminococcus bromii* L2–36	GCF_002834165.1	Food allergy	[38]

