**Fig. 2 fig0002:**
[figure not shown]
Flow Chart of the participant selection process in the iTARGET study.

To take part of the study, volunteers must complete the participant journey and collect a compliant stool sample. The study will be carried out in two phases. In the first phase (T0), stools from healthy participants will be collected, with a diversified diet rich in fiber, validated by a questionnaire carried out during the selection visit. Each participant will make one stool donation. This collection will permit the identification of carriers for bacteria of interest in relation to their diet and the development of targeted culturomics tools. In a second phase (T0+1 year), individuals selected according to their microbial profiles (*n* = 3) obtained from shotgun metagenomics at T0 in relation to their diet and whose stools presented the bacteria of interest (Table 1) will be recalled for a new stool donation in order to carry out culturomics using tools designed during the first phase (Fig. 1).

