### Final visit at 12–18 months for three selected subjects

Based on metagenomic analyses and dietary profiles of the samples from the first phase (T0), three subjects will be recalled for a new stool collection. The subjects will be selected based on their most distinct metagenomic profiles and the detection of the selected species of interest (Table 1). The selection criteria will be checked again for each selected volunteer. The participants will again complete the questionnaires used for recruitment. If the subjects still meet the selection criteria, new stool collection kits will be distributed to them.

Samples that do not pass the initial quality control (e.g. presence of identification data on tube, missing sample, broken tube, etc.) are flagged up and a new sampling is given. QC-validated samples are stored at −80 °C at the MetaGenoPolis-SAMBO BRC (Biological Resources Centre), which is ISO9001 certified and labelled GIS-IBiSA (CRB N°242), until further processing.

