### Data analysis and outcomes

Subjects will be included chronologically and successively as soon as they meet the inclusion criteria and have given their consent to participate. The monocentric nature of the study, the small number of subjects and the expertise of the UEN staff involved in the study will limit the number of missing data. Data will be collected using observation notebooks specific to the study, using the Skezia software with secure access (https://skezia.io/). The software allows quality control of the data and monitoring of modifications, with the date and name of the person who made the modifications.

Our primary outcome is the isolation and culture of at least one isolate of each species of interest, previously identified by metagenomic data analysis and literature review (Table 1). The metagenomic identification of additional bacterial species of interest will rely on the bioinformatical and biostatistical of the French Milieu Intérieur cohort [47] for which we have obtained the consortium's agreement for use within the strict framework of this project (see iTARGET in https://www.milieuinterieur.fr/en/about-us/collaborations/), and additional public shotgun metagenomic datasets [10].

The secondary outcomes will be to first obtain metagenomic profiles of the faecal microbiota using a high throughput shotgun sequencing strategy [48] in order to identify the participant carriers for bacteria of interest in relation to their dietary profiles [10,49,50]. Combined analysis of metagenomic data, health records and diet profiles will be performed under the R software (version 3.6) [51]. Second, we aim to acquire phenotypic and genetic and/or genomic characteristics of the isolates, including growth parameters, production of bacterial metabolites, general sugar metabolisms, 16S rDNA sequencing and functional potential through genome annotation. We will collect and characterize at least one strain per donor and per media for the selected species of interest (Table 1).

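### The primary aim includes never-cultured species, but the recall detection criterion, the sample size and the body-text primary outcome refer only to Table 1, and the abstract defines success differently again

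*Protocol article*

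**What the plan says.** The protocol article describes the target of the study in several places.

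- **Study aims.** The primary aim is isolation from stools of high-fiber participants, "comprising new isolates of known species (list of selected species in Table 1) or new species for which no isolates have yet been cultured". The two routes are joined by an *or* and carry no weights.
- **Abstract.** "Our primary outcome is the isolation and culture of at least one potentially beneficial isolate". There is no limit to Table 1.
- **Data analysis and outcomes.** "Our primary outcome is the isolation and culture of at least one isolate of each species of interest, previously identified by metagenomic data analysis"; the sentence goes on to cite literature review and Table 1. The next sentence adds: "The metagenomic identification of additional bacterial species of interest will rely on the bioinformatical and biostatistical of the French Milieu Intérieur cohort", together with public datasets. The section closes with a target of at least one characterized strain per donor and per medium, again for the Table 1 species.
- **Participants' recruitment (text under Fig. 2).** The three phase 2 donors are people chosen on microbial profile in relation to diet and "whose stools presented the bacteria of interest (Table 1) will be recalled for a new stool donation".
- **Final visit at 12–18 months.** "The subjects will be selected based on their most distinct metagenomic profiles and the detection of the selected species of interest (Table 1").
- **Sample size.** The binomial calculation covers the 19 species of Table 1.

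**The concern.** The aim is wider than the rules meant to deliver it. By the aim's own sentence, Table 1 is the known-species list. Where the plan names species for recall, for sample size or for the body-text primary outcome, it names that list only. A first isolate of a never-cultured species would serve the stated aim and would meet the abstract's outcome. It would not count under Data analysis and outcomes.

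Two things are at stake. First, the final report could claim or deny success on the same results, depending on which section is used. One new isolate of any potentially beneficial species meets the abstract's outcome. The body text requires an isolate of every Table 1 species and gives no credit for a new one. Second, the Background rests the study's novelty on using positive donor selection to isolate new species, and phase 2 culturomics uses only three recalled donors. The recall rule as written does not direct any of those places to a carrier of a specified uncultured species, even where the planned T0 shotgun data would reveal one.

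**Working it through.** **1. Scope of each statement, side by side**

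| Section | Species covered | Would a first isolate of an uncultured species count? |
|---|---|---|
| Study aims | Table 1, or never-cultured species | Yes |
| Abstract, primary outcome | Any potentially beneficial isolate | Yes |
| Data analysis and outcomes, primary outcome | Each Table 1 species | No, as written |
| Data analysis and outcomes, strain target | Table 1 | No, as written |
| Recall rule (two sections), detection element | Table 1 | Not used |
| Sample size | Table 1 | Not used |
| Data analysis and outcomes, additional species | Outside Table 1 | Not linked to recall or to the primary outcome |

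**2. Content of Table 1.** Of 19 rows, 8 carry a DSM number, 4 an ATCC number and 2 an NCTC number: 8 + 4 + 2 = 14. The other five are *B. longum* spp., *A. hadrus* BPB5, *C. catus* AF45–17, *R. inulinivorans* 2789STDY5608835 and *R. bromii* L2–36. All 19 are named species with an accession number, and none is presented as uncultured.

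**3. The plan's own figure.** The Sample size section gives 4.4 ± 6.3 individuals (mean ± SD) in the high-fiber group. Mean plus one SD is 4.4 + 6.3 = 10.7, consistent with the stated minimum of 10 if truncated (11 if rounded up). The 19 prevalences are not given, so the per-species numbers cannot be rebuilt. The figure concerns Table 1 species only.

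**4. Illustration for a species outside Table 1.** The documents give no prevalence for any uncultured species, so the prevalences p below are assumptions. The chance of at least one carrier among n donors is 1 − (1 − p)^n.

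| Assumed p | n = 3 (recall unrelated to carriage) | n = 10 (all T0 donors) |
|---|---|---|
| 5% | 1 − 0.95³ = 0.14 | 1 − 0.95¹⁰ = 0.40 |
| 10% | 1 − 0.90³ = 0.27 | 1 − 0.90¹⁰ = 0.65 |
| 20% | 1 − 0.80³ = 0.49 | 1 − 0.80¹⁰ = 0.89 |
| 30% | 1 − 0.70³ = 0.66 | 1 − 0.70¹⁰ = 0.97 |
| 50% | 1 − 0.50³ = 0.875 | 1 − 0.50¹⁰ = 0.999 |

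If recall could use T0 detection of one given species, the chance that a carrier is among the three recalled rises from the middle column toward the right-hand one. The right-hand column is an upper limit: it supposes that a carrier is detected, still carries the species a year later, remains eligible and is given a place. For a probability of 0.95, p must be at least 1 − 0.05^(1/3) = 63.2% with three unselected donors, against 1 − 0.05^(1/10) = 25.9% with ten.

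**The case against.** A reader might infer that half of the aim is neither enriched for nor scored. The documents do not support that, for these reasons.

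- **Scoring.** The abstract's outcome would score a new species. In Data analysis and outcomes, the sentence on additional species directly follows the primary outcome and uses the same term, species of interest. The first secondary outcome, identifying carriers of bacteria of interest in relation to diet, is not limited to Table 1.
- **Enrichment.** All donors are selected for high fiber intake, which the Background connects to isolating new species. The recall rule also uses the most distinct metagenomic profiles, and diet as well. A donor with an unusual profile can qualify on that ground, so it is not established that a carrier of an uncultured species has no claim to a place. No minimum number of Table 1 species is set. An SD of 6.3 around a mean of 4.4, with a floor of 1, suggests that many Table 1 species are common and that the detection condition excludes few donors; this is inference, since prevalences are not given.
- **Half.** The two routes are alternatives without weights, so known species alone can satisfy the aim.
- **Interpretability.** A failure to isolate a new species would not be uninterpretable, because T0 shotgun profiles can show what each recalled donor carried at T0.
- **Missing material.** Fig. 1, cited at the new-species clause, is not shown and may depict a route for such species. An article also leaves detail to the full protocol.

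All of this limits the point; none of it removes it. Fiber intake and a distinct profile do not identify a carrier of a specified species. The abstract's wider outcome adds to the inconsistency. The recall rule and the primary outcome are stated explicitly and more narrowly than the aim, so the mismatch is not merely detail left to another document. Whatever Fig. 1 shows would still have to agree with that text.

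**Conclusion.** The point holds as a mismatch of scope. The abstract, Study aims and Data analysis and outcomes define success differently. Followed as written, the recall rule does not specifically select for never-cultured species, and the body-text primary outcome does not count them. None of the 19 species used for detection at recall is presented as uncultured. No section shown links the planned additional species to recall or to the primary outcome.

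The practical cost cannot be fixed from the documents. At assumed prevalences of 10% and 20%, the chance of a carrier among the three recalled donors is 0.27 and 0.49 if recall is unrelated to carriage, against at most 0.65 and 0.89 if T0 detection among ten donors could guide recall. These figures are for one species and are context only; the finding rests on the wording. It should be corrected, but it does not undermine the known-species part of the study.

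**What to change.** Reconcile the abstract, Study aims and Data analysis and outcomes into one primary outcome. Then take one of two routes.

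1. **Keep uncultured species in the aim.** Fix the list of additional or uncultured species of interest, from the Milieu Intérieur cohort and the public datasets, before T0 profiles are used for recall. Amend both statements of the recall rule so that detection refers to Table 1 plus that list. Report two counts: Table 1 species with a new isolate, and listed uncultured species with a first isolate.
2. **Do not target them.** Remove uncultured species from the primary aim.

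Either route is mainly a change of wording, since the in-silico identification and the T0 shotgun sequencing are already planned. The small downside of the first route is that a recall place may go to a donor with slightly fewer Table 1 species.

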**Fig. 1 fig0001:**
[figure not shown]
Overall strategy of the iTARGET study.

### Study design

The iTARGET cohort is a monocenter, prospective, observational study of adults with healthy lifestyle and high daily fiber consumption. The recruitment period starts September 2023 and ends December 2024.

### Eligibility criteria

Volunteers will be selected from adults individuals, with a healthy lifestyle, i.e. a state considering both diet and physical activity, and consuming (i) a daily fiber consumption of >25*g* per day (a value comprised between the recommendations of the French Agency for Food, Environmental and Occupational Health & Safety (ANSES) of 30*g*/day [39] and the current daily consumption of the French population of 20*g* fiber per day (INCA3 study) [40]) (ii) a daily variety of fiber following the recommendations of the French National Nutrition and Health Program (Programme National Nutrition Santé PNNS), consisting of >5 portions of fruit and vegetables per day [41] and (iii) in compliance with the eligibility criteria defined below.

### Inclusion criteria

•Healthy adult individuals•Age: ≥ 20 and ≤ 50 years old•BMI: > 18.5 and < 25 kg/m^2^•Intake of at least 25*g* of dietary fiber per day•Consumption of >5 portions of fruit and vegetables a day•A diversified diet low in ultra-processed foods

### Non-inclusion criteria

•Known pathologies•Current treatment•Antibiotics and/or transit modulators taken 3 months prior to sampling•History of digestive surgery having an impact on the microbiota incompatible with the study (bariatric surgery)•Consumption of food supplements based on protein preparations, probiotics or prebiotics•Smoking•Alcohol consumption: > 2 glasses (i.e. 20 g) per day•Sedentary lifestyle (< 600 Mets/min/week) or intense sport activity (≥ 3000 Mets/min/week)•Pregnant or breast-feeding women•Persons under legal protection (curatorship, guardianship, etc.)•Volunteers taking part to interventional study•Person refusing to be registered on the National Register of Healthy Volunteers of the Ministry of Health (VRB)•Subject not affiliated to the French social security system•Subject in a period of exclusion from a previous study or having received a total amount of 6000 euros over the 12 consecutive months preceding the start of the trial

